### Principal components analysis

Principal components analysis will be used to categorize caregivers according to wealth quintile using established methods [52],[53]. While no established rules exist for selecting variables, broad categories of assets will include durable asset ownership, housing characteristics, and access to basic services based on precedent [52]. To avoid illogical rankings [54], only those variables with a prevalence between 5%–95% will be retained. While these thresholds are arbitrary, they are consistent with rules of general inference to define a value with low probability. Eigenvalues will be generated in Stata, which represent linear combinations of variables that capture the maximum amount of remaining uncertainty in the data for each component. The component with the greatest eigenvalue will be selected for creating a wealth index, as higher order components have been shown not to be important in a previous study and convention has become to create wealth indices on only one component [52]. Factor loadings will be assessed to determine what variables align the most closely with the principal component and evaluate whether its representation of wealth has face validity. Caregivers will be divided into quintiles, and variables for regression analyses will be based on these quintiles. The scale will be validated according to a Cronbach’s alpha greater than 0.6.

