**Table 3 Tab3:** **Variables to be tested**

Conceptual framework category	Parameter	Description
Demographic characteristics	Household size	Continuous variable (min = 2 people, max = 23 people in Gujarat and 32 in Uttar Pradesh)
	Child sex	Male =0, female =1
	Child age	Continuous variable (min =2 months, max =59 months)
Characteristics of the social structure	Mother’s education	No or primary education =0, primary education or above =1, secondary education or above =2, tertiary education or above =3
	Father’s education	No or primary education =0, primary education or above =1, secondary education or above =2, tertiary education or above =3
	Scheduled caste	Not a scheduled caste =0, scheduled caste =1
	Scheduled tribe	Not a scheduled tribe =0, scheduled tribe =1
	Other backwards caste	Not another backwards caste =0, other backwards caste =1
Caregiver knowledge	Knowledge about ORS	No knowledge =0, knowledge =1
	Knowledge about zinc	No knowledge =0, knowledge =1
Enabling factors	DAZT program	Initial survey, final survey
	Below poverty line card	No BPL card =0, BPL card =1
	Very poor	Any other wealth quintile =0, second wealth quintile =1
	Poor	Any other wealth quintile =0, third wealth quintile =1
	Less poor	Any other wealth quintile =0, fourth wealth quintile =1
	Least poor	Any other wealth quintile =0, fifth wealth quintile =1
Need factors	Duration of diarrhea	Continuous variable (min = 0 days, max = 15 days in Gujarat and 32 in Uttar Pradesh)
	Blood in the stool	No blood in the stool =0, Blood in the stool =1
Treatment seeking	Seek treatment outside of the home	No treatment sought outside of the home =0, treatment sought =1
Treatment given	Given ORS	No ORS =0, given ORS =1
	Given zinc	No zinc =0, given zinc =1

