### Net-benefit regression-based approach to cost-effectiveness analysis

A second approach to calculating cost-effectiveness will be taken according to net-benefit regression methods to control for imbalances in covariates arising from the non-randomized study design [21],[31],[32]. This method uses patient-level data of economic costs to caregivers and health outcomes, distributing program costs from the last year of the program evenly across children in the endpoint survey. A modification of the net-benefit statistic will serve as the dependent variable, given that outcomes are measured in terms of a health gap measure instead of health expectancy measure [50]. This formulation adds costs to outcomes expressed in monetary terms instead of taking the difference as is done in standard net-benefit calculations. The coefficient on a treatment variable that distinguishes between the starting point and endpoint of the program will be used to represent incremental net benefit. One sided *p*-values from the treatment variable will be used to construct CEACs, using results from a series of regressions that use different values for the ceiling ratio. Due to the non-normality in the distribution of residual values, a generalized linear model using a gamma distribution will be used. Huber-White robust standard errors will be used to address heteroskedasticity, and clustering will be accounted for consistent with study design. Data will be checked for non-linearities to assess whether use of a spline term improves model fit. The importance of influential data points will be checked using DFBETAs, excluding caregivers with the top ten DFBETA scores in sensitivity analysis. Calculations will be performed in Stata 13, using standards for good practice for using statistical regression models in economic evaluations [51].

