Secular trends such as improvements in living conditions, access to safe water, and improved sanitation may have contributed to the decline in diarrhea prevalence in the DAZT study area [60]. However, secular trends may be less relevant for costs as economic growth is unlikely to drive prices for diarrhea treatment down. In addition, this study design is sensitive to sudden changes in the conditions of the study area [61]. The Hawthorne effect is a potential confounder, which would overstate the magnitude of the effect [48]. Regression towards the mean may be problematic [58], which means that if a study had high diarrhea prevalence at beginning, future measurements will be likely to be less extreme. The DAZT study found a 14% prevalence of diarrhea in 2011, while levels were 13% in 2005/6 in Gujarat [36] and were 9% nationwide [7]. Regression to the mean predicts that the prevalence would be lower in future surveys as downward changes would be more frequent than upward changes.

Limitations exist in that household data is based on self-report, reporting bias could have occurred, and long-term outcomes and programmatic outcomes such as quality are not measured. Some researchers argue that only children who receive the recommended 10–14 day course should be included in analysis. However, in the DAZT program, most children only received partial courses of zinc in addition to antibiotics and anti-diarrheal medications. Seasonal effects are possible given that each survey was given at a different point in the monsoon cycle across the years of the study. Limitations of principal components analysis are recognized, such as not evaluating the quality of assets, assuming the first principal component to be an adequate indicator of socioeconomic status, being a relative measure, and producing quintiles with variable arrays of asset ownership [53],[62],[63]. Finally, outcomes will not be evaluated according to severity, which could lead to outcomes such as children with fewer symptoms or shorter episodes having more favorable cost-effectiveness.

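### Housing, water and sanitation, named as rival explanations for fewer episodes, can enter the net-benefit regression only through a relative wealth rank, which does not hold their change between surveys constant

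*Protocol article*

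**What the plan says.** Under Strengths and limitations the article concedes: "Secular trends such as improvements in living conditions, access to safe water, and improved sanitation may have contributed to the decline in diarrhea prevalence". The reply that follows concerns costs only (economic growth is unlikely to push treatment prices down). No reply is given for episodes, which are the outcome of the net-benefit regression.

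That regression is introduced "to control for imbalances in covariates arising from the non-randomized study design". Its effect estimate is a survey contrast: "The coefficient on a treatment variable that distinguishes between the starting point and endpoint of the program will be used to represent incremental net benefit".

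Table 3 lists the covariates: household size, child sex and age, parental education, caste and tribe, knowledge of ORS and zinc, a poverty-line card ("No BPL card =0, BPL card =1"), four wealth dummies (the first coded "Any other wealth quintile =0, second wealth quintile =1"), duration, blood in stool, treatment seeking and treatment given. The Conceptual framework section says the framework variables stay in the models whether or not they are significant.

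Housing and services appear only under Principal components analysis: "broad categories of assets will include durable asset ownership, housing characteristics, and access to basic services based on precedent". Then "The component with the greatest eigenvalue will be selected for creating a wealth index", and caregivers are divided into quintiles for the regressions. The limitations section concedes that the index is relative and rests on the first component.

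**The concern.** The treatment variable is the survey itself, so programme effect and calendar time share one coefficient. A household condition that affects diarrhea and changed between the surveys can be separated from the programme only if it is held constant in the model. By Table 2 the endpoint survey began about 2.5 years after the start survey in Gujarat (March 2011 to September 2013) and about 3.4 years after it in Uttar Pradesh (April 2011 to August 2014), long enough for such conditions to change.

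A wealth quintile does not do this. Two households in the same quintile can differ in dwelling, water source and toilet, and the share with each can move over time while the quintiles stay the same size. If conditions improved, the resulting fall in episodes would be credited to DAZT. The adjustment is what the article offers as this method's advantage over the simulation, and here it does little about explanations the article itself raises.

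**Working it through.** The article gives no figure on this point, so there is none to reproduce. The check is a comparison of sections, followed by two illustrations on assumed inputs.

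**1. Named causes against the covariate list.**

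| Cause named in the limitations | Own row in Table 3 | Other route into the regression |
|---|---|---|
| Living conditions | No housing row | Housing characteristics, inside the wealth index |
| Safe water | No | At most through basic services, inside the index |
| Sanitation | No | At most through basic services, inside the index |

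The poverty-line card, parental education, caste and household size are general markers of living standard. None measures water, sanitation or housing. Index items outside 5% to 95% prevalence are dropped, so a very common or very rare item might not enter even the index.

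**2. What the rank can hold constant.** If quintiles are cut within each survey, each survey holds about 20% of caregivers per quintile by construction. The dummies are then balanced across surveys and cannot absorb a shift common to all households. If they are cut on pooled data, the rank can move with time, but only as far as the blended component moves. The article does not say which is meant.

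**3. Simulation with no programme effect.**

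- From the article: Gujarat survey sizes 4,200 and 5,080 (Table 2) and 14% starting prevalence (Strengths and limitations).
- Assumed: unsafe water and unsafe sanitation each fall from 60% to 50%, 40% or 30%; each carries an odds ratio for diarrhea of 1.3 or 1.6; the index is the first component of ten binary items (eight durable assets, water, sanitation).
- Model: logistic regression of the episode on the survey indicator. The correct odds ratio is 1.00.

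| Unsafe share | OR per item | Unadjusted | Quintiles within survey | Quintiles pooled | Water and sanitation entered directly |
|---|---|---|---|---|---|
| 60% to 50% | 1.3 | 0.949 | 0.949 | 0.954 | 1.000 |
| 60% to 50% | 1.6 | 0.913 | 0.913 | 0.921 | 1.000 |
| 60% to 40% | 1.3 | 0.901 | 0.901 | 0.911 | 1.000 |
| 60% to 40% | 1.6 | 0.832 | 0.832 | 0.848 | 1.000 |
| 60% to 30% | 1.3 | 0.854 | 0.854 | 0.870 | 1.000 |
| 60% to 30% | 1.6 | 0.755 | 0.754 | 0.779 | 1.000 |

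Within-survey quintiles remove essentially none of the bias. Pooled quintiles remove about 10% to 12% on the log-odds scale; in the last row, 1 − ln(0.779)/ln(0.755) = 1 − 0.250/0.281 = 0.11. The pooled result depends on the assumptions. When I let durable assets rise along with water and sanitation, pooled quintiles absorbed far more, while within-survey quintiles still absorbed nothing.

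**4. Size on the prevalence scale (all inputs but the 14% assumed).** With share p0 having improved sanitation at the start, p1 at the end, and relative risk RR, the endpoint prevalence is 0.14 × (1 − p1(1 − RR)) / (1 − p0(1 − RR)).

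- p0 = 0.3, p1 = 0.4, RR = 0.9: 0.14 × 0.96/0.97 = 13.86%, a relative fall of 1.0%.
- p0 = 0.3, p1 = 0.5, RR = 0.8: 0.14 × 0.90/0.94 = 13.40%, a relative fall of 4.3%.
- p0 = 0.4, p1 = 0.6, RR = 0.7: 0.14 × 0.82/0.88 = 13.05%, a relative fall of 6.8%.

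**The case against.** The best defence is disclosure. The article calls exposure to secular trends part of its main limitation, names these very conditions, admits that the index is relative, and accepts limits on policy conclusions. It claims to control covariate imbalance and nowhere claims that the regression removes secular trends. All of that stands, and the point is therefore not a contradiction. Disclosure does not, however, explain why housing and service items recorded for the index are kept out of the one model built to adjust.

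Four stronger readings are tempting and are not supported.

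- **That water source and toilet type are known to be held.** No section names them. Basic services is the only wording that could cover them, and the Sampling and data collection section mentions neither.
- **That the simulated odds ratios or the 1.0% to 6.8% range estimate this study's bias.** They rest on assumed shifts and effects, and on a prevalence or logistic episode model rather than the planned gamma model on net benefit. The Conceptual framework section limits the model to children who sought care, and the subgroup section notes that reduced treatment seeking would count as episodes averted, so the modelled outcome may not track prevalence. The prevalence figures also let the other covariates absorb nothing.
- **That both methods are affected.** The health outcome in the Monte Carlo analysis comes from ORS and zinc coverage entered into LiST, not from observed episodes.
- **That the index must be rebuilt from durable assets.** Direct covariates can be added without redefining it, and its present make-up follows cited precedent.

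It could also be said that Table 3 is not a closed list, being titled as variables to be tested and cited for descriptive statistics. That has little force, since the framework variables are to be included regardless of significance and no water, sanitation or housing variable is among them.

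**Conclusion.** The concern holds for the net-benefit regression. The article names living conditions, safe water and sanitation as possible causes of fewer episodes, gives them no covariate of their own, and lets housing and basic services in only through a one-component quintile rank. Such a rank does not hold their change between surveys constant, so any effect on episodes stays largely in the start/endpoint coefficient. This is firm if quintiles are cut within each survey. If they are pooled, it depends on how far the blended component moves with these conditions.

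The direction favours the programme if conditions improved. The size cannot be given from the article. This is an acknowledged limitation that the plan could reduce at little cost, and it should be addressed.

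**What to change.** Add to the net-benefit regression, as forced covariates, the housing and basic-service items already recorded for the wealth index, with water source and toilet type among them if they were collected and coded alike in both surveys. Report the treatment coefficient with and without these terms, so that readers see how much of the effect survives. Leave the wealth index as defined, and state whether its quintiles are cut within each survey or on pooled data.

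The cost is a few more parameters in surveys of 1,001 to 5,080 participants at the start and endpoint, and some collinearity with the quintile dummies, which matters little because their coefficients are not the target. If the water and toilet items were not collected, the change is limited to what was recorded, and the article should say so. Unmeasured trends would remain, as would the seasonal difference between surveys (start surveys March to June, endpoint surveys August to November), so the coefficient would still need to be read as an uncontrolled before-and-after contrast.

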### Ethical approval and study status

For the main study, ethical approval was obtained from SAS and the Johns Hopkins Bloomberg School of Public Health (JHSPH) Institutional Review Board (IRB). DAZT project activities commenced in late 2010 and will span through 2014.

## Discussion

Economic evaluation provides insights into the appropriate allocation of resources, and yet the number of cost-effectiveness and cost-utility analyses alongside programs at scale - where large amounts of resources are invested - remains limited. When planning these studies, differences in methods adopted have implications on the validity of findings and on their generalizability. Economic evaluation has traditionally focused on the cost of an intervention to produce a desired health outcome in studies based on modeled evidence or data collected alongside randomized controlled trials. As the number of interventions with known impact on health increases, there is an increased need for evidence on ways of operationalizing delivery of these health services to ensure high coverage, quality, and cost-effectiveness.

The aims of the DAZT intervention are to improve the supply, demand, and prescribing practices for treatment of diarrhea in children with zinc and ORS. These objectives are consistent with goals of The Indian Academy of Pediatrics [55], WHO [56], and UNICEF [3] who have all endorsed zinc supplementation to ORS for the treatment of diarrhea in children. In addition, the Government of India has established the Oral Rehydration Therapy Program to increase awareness about causes of diarrhea and its treatment among mothers and communities [7], and results of this study may be used to support this program.

This study will provide an evaluation of a zinc delivery strategy in a resource-constrained setting, in addition to a comparison of methods for cost-effectiveness analysis. The calculation of results using two different methods will provide evidence about the robustness of results, while informing broader discourse on methods for carrying out economic evaluations alongside programs delivered at scale. Each method has its strengths and limitations. The Monte Carlo Simulation with patient level data approach will allow for the incorporation of uncertainty around program costs and is a more widely used technique than the net-benefit regression approach. The net-benefit regression framework will allow for cost-effectiveness to be calculated controlling for other factors, which are unbalanced across arms in this study. Comparing the two analytical approaches will stimulate discussion about when analysts should choose one over the other when planning their analyses, particularly in the context of evaluation of programs at scale.

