**Methods/Design:**

This study evaluates the cost-effectiveness of DAZT program activities relative to status quo conditions existing before the study, comparing a Monte Carlo simulation method with net-benefit regression, discussing the strengths and weaknesses of each approach. A control group was not included in the ‘before and after’ study design as zinc has proven effectiveness for diarrhea treatment. Costs will be calculated using a societal perspective including program implementation and household out-of-pocket payments for care seeking, as well as estimates of wages lost. Outcomes will be measured in terms of episodes averted in net-benefit regression and in terms of the years of life lost component of disability-adjusted life years in the method based on Monte Carlo simulation. The Lives Saved Tool will be used to model anticipated changes in mortality over time and deaths averted based on incremental changes in coverage of oral rehydration salts and zinc. Data will derive from cross-sectional surveys at the start, midpoint, and endpoint of the program. In addition, Lives Saved Tool (LiST) projections will be used to define the reference case value for the ceiling ratio in terms of natural units.

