### Sample size and power calculation

The sample size for the main effects study was calculated according to standard methods for rates calculated through cluster randomized designs. Calculations used ORS coverage rates in the initial survey since very few children received zinc before the start of the program, and delivery of ORS and zinc were assumed to be linked. Actual sample sizes achieved for each survey are presented in Table 2. Using sample sizes from the main study, power to detect meaningful differences will be calculated for our cost-effectiveness estimate. Two formulas from Glick et al. [39] will be merged to determine power for cost-effectiveness using a novel approach to calculating the reference case ceiling ratio from an estimate based on per capita gross national income (GNI) and Lives Saved Tool (LiST) outputs of deaths averted/episodes averted.

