### Costing

The cost of the DAZT program from 2011 to 2013 (Gujarat) and 2014 (Uttar Pradesh) will be calculated from the societal perspective according to Saving Newborn Lives guidelines and standard textbooks [20],[40],[43]. The societal perspective reflects the incremental costs incurred by implementing agencies, government providers, and households. Program costs will be divided into capital costs and recurrent costs, with data derived from program records, primary sources, and interviews with individuals responsible for implementation. Capital costs will be annualized and discounted according to a rate of 3% according to the standard rate for economic evaluation in International Health [44]. Consumer price indices from the International Monetary Fund (IMF) will be used to inflate costs to 2014. Costs will be converted to US$ using exchange rates from OANDA.com. Incremental government provider costs will be derived using reported estimates of time spent on the provision of diarrhea treatment services by public sector providers. Economic costs to caregivers for diarrhea treatment of the episodes in the last 2 weeks will be evaluated according to data collected through household questionnaire and consist of direct medical costs of treatment, direct non-medical costs (transportation), and indirect costs (wages lost by caregivers) [45]. No adjustments will be made to collected data to approximate opportunity costs.

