### Health outcomes

In the standard cost-effectiveness calculation, health outcomes will be derived from incremental changes in coverage measured in cross-sectional household surveys and inputted into LiST. LiST will estimate the incremental number of lives saved from the study’s start to its completion. The years of life lost (YLL) component of disability-adjusted life years (DALYs) will be calculated using the standard formula from the Global Burden of Disease study [46]. A life expectancy estimate will be taken from WHO life tables representing the midpoint between 1–4 years old. A discount rate of 3% will be used in reference case calculations, and age weighting will not be used to be consistent with the Disease Control Priorities Project second edition (DCP2) [41]. Long-term sequelae such as acute cognitive and psychomotor development effects in young children, the effects of diarrhea on stunting [4], and obesity and related conditions that can occur later in life (cardiovascular disease and diabetes) [47] were not measured and will not be considered. The net-benefit regression approach will be limited to episodes averted as it is impossible to know the specific long-term health outcomes for individual patients. Limitations of drawing data from a single uncontrolled study are recognized [48], although cost-effectiveness analysis is often conducted on data from a single effectiveness study, and conditions in the study sites are not atypical of other relevant settings in low- and middle-income countries.

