### Monte Carlo Simulation with patient level data approach to cost-effectiveness analysis

Initial cost-effectiveness calculations will be generated through Monte Carlo simulation to evaluate uncertainty in economic costs to caregivers and health outcomes, using an additional simulation technique to account for the uncertainty in program costs. Samples of economic costs to caregivers and health outcomes will be drawn from the data equal in size to the number of data points, with replacement. Uncertainty around program costs will be simulated by drawing data from gamma distributions derived from most likely, low and high estimates for each component. This process will be repeated 10,000 times to ensure that tails of standard error distributions are filled and increase stability in results since available computing power is sufficient. ICERs will be calculated, and uncertainty will be quantified using a bootstrap approach, choosing the values representing the upper and lower 2.5% of data. To disambiguate negative ICERs and show the probability of cost-effectiveness according to different values of the ceiling ratio, CEACs will be calculated, using per capita GNI as the reference case threshold [49] (US$1,740 in Gujarat, $571 in Uttar Pradesh). Calculations will be performed using Microsoft Excel with the Palisade at-risk add-in.

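### The two cost-effectiveness methods also differ in outcome and, apparently, in program-cost window, so comparing them cannot isolate the effect of method and supports robustness only weakly

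*Protocol article*

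**What the plan says.** The Discussion of the protocol article gives the reason for running two analyses: "The calculation of results using two different methods will provide evidence about the robustness of results". Strengths and limitations calls this the study's main strength. The Discussion adds that the comparison should prompt debate about when to choose one method over the other.

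The inputs are set out elsewhere in the article:

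- **Outcome.** The abstract states: "Outcomes will be measured in terms of episodes averted in net-benefit regression and in terms of the years of life lost component" for the Monte Carlo method. Under Health outcomes, for the standard calculation, "health outcomes will be derived from incremental changes in coverage measured in cross-sectional household surveys and inputted into LiST", while "The net-benefit regression approach will be limited to episodes averted".
- **Program costs.** Under Costing, "The cost of the DAZT program from 2011 to 2013 (Gujarat) and 2014 (Uttar Pradesh) will be calculated from the societal perspective". The net-benefit regression section is narrower, "distributing program costs from the last year of the program evenly across children in the endpoint survey". The Monte Carlo section names no cost years and says: "Uncertainty around program costs will be simulated by drawing data from gamma distributions derived from most likely, low and high estimates".
- **Covariates.** Only the regression adjusts for them.

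**The concern.** Comparing two methods tells the reader about the methods only if the inputs are the same, or if the effect of changing the inputs can be separated out. Here the outcome, and it seems the program-cost years, change together with the method. No run is described in which they are held equal.

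If the two analyses disagree, the reader cannot tell whether the cause is covariate adjustment, the treatment of cost uncertainty, the outcome or the cost window. If they agree, differences in inputs may have offset each other. What is at stake is the article's methodological aim and its claimed main strength. Either analysis can still be read on its own terms.

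**Working it through.** The plan states no figure that this point depends on, so the check sets the two specifications side by side.

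| Feature | Monte Carlo simulation | Net-benefit regression | Part of the intended contrast? |
|---|---|---|---|
| Covariate adjustment | none | yes | yes (Background, Discussion) |
| Program-cost uncertainty | gamma draws per component | none; spread evenly over endpoint children | yes (Background, Discussion) |
| Outcome | years of life lost, modelled through LiST from coverage change | episodes averted, from survey data | no |
| Program-cost years | no limit stated; Costing covers 2011–2013 (Gujarat) or 2011–2014 (Uttar Pradesh) | last year only | no |
| Ceiling ratio | per capita GNI, US$1,740 and $571 | in natural units, from GNI and LiST outputs; varied over a series of values | follows from the outcome |

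**Step 1: what the authors set out to contrast.** Both the Background and the Discussion describe the trade-off as covariate control (regression) against simulated program-cost uncertainty (Monte Carlo). Outcome and cost years are not part of that account.

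**Step 2: can the outcome difference alone move the result?** By the article's own account, yes.

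- Strengths and limitations warns that diarrhea prevalence may have fallen through secular trends and regression to the mean, and that the surveys fell at different points of the monsoon cycle.
- Table 2 shows starting surveys between March and June and endpoint surveys between August and November.
- The section on targeting by subgroup admits that, by provider, less treatment seeking would show up as episodes averted.
- The LiST result is driven by change in ORS and zinc coverage instead. The two outcomes can therefore move apart whichever analytic method is used.

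**Step 3: how far apart could the cost bases be?** This assumes that the simulation uses the whole costing window, which the article does not say outright. Let s be the last year's share of total program cost. The ratio of all-years to last-year cost is 1/s.

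- Equal yearly spending (assumption): Gujarat 1/(1/3) = 3; Uttar Pradesh 1/(1/4) = 4.
- Last-year share between 0.5 and 1.5 times the equal share (assumed range): Gujarat from 1/0.167 = 6 down to 1/0.5 = 2; Uttar Pradesh from 1/0.125 = 8 down to 1/0.375 = 2.7.

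These ratios describe the cost bases only. Health outcomes has LiST estimate lives saved from the start of the study to its completion, so costs over several years would be set against effects over several years.

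**Step 4: is there a bridging run?** The article describes none: no simulation on episodes, no regression on the full cost window and no regression without covariates.

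**The case against.** The strongest reply is that the article claims little. It promises evidence about robustness and a discussion of method choice, and its Background presents alternative methods as a test of structural uncertainty. Two differently built analyses reaching the same verdict would be real, if weak, support. Health outcomes also explains the restriction to episodes: long-term outcomes of individual children cannot be known. All of this stands, and it is why agreement should be called weak support rather than no support.

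A reader might also infer stronger things that the article does not support:

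- **That nothing is held constant.** The before-and-after contrast, the household surveys, the caregiver cost data, the societal perspective and the price basis are shared.
- **That covariate adjustment is a further defect.** It is one of the contrasts under study.
- **That the ceiling is another independent difference.** A per-episode outcome cannot use a threshold per year of life lost. The natural-unit ceiling converts the same GNI anchor, and the acceptability curves vary it.
- **That the conversion leaves out years of life lost per death, or that ORS inflates the value of an episode.** The first rests on a one-sentence summary in a condensed article, and Health outcomes describes how years of life lost are calculated. On the second, the Background credits ORS with lower prevalence as well as fewer deaths, and the deaths and episodes averted in the ceiling both come from LiST.
- **That cost-effectiveness is distorted threefold or fourfold.** The Monte Carlo cost years are inferred, and the effect windows differ along with the cost windows.

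**Conclusion.** The point holds in a limited form. The difference in outcome is explicit. The difference in cost window is a reading of the article: the regression is confined to the last year, while the simulation carries no such limit and the general costing spans three or four calendar years. With no matched run, a disagreement cannot be assigned to the analytic method, and an agreement shows only that two differently built analyses reach the same verdict.

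The effect on the results cannot be sized from the article. It depends on yearly spending, the LiST output and the survey episode counts, none of which are given. Neither analysis is invalidated. This is a worthwhile and inexpensive improvement to the study's ability to answer its own methodological question.

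**What to change.** For each state, add one bridging simulation that applies the Monte Carlo method to survey episodes averted, with the same program-cost years and the same range of per-episode ceilings as the regression. Run the regression both with and without covariates. State the simulation's cost years explicitly. The four results then form a ladder:

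1. Planned simulation against bridging simulation: effect of outcome (with its ceiling scale) and cost window.
2. Bridging simulation against unadjusted regression: effect of the estimation approach, including program-cost uncertainty.
3. Unadjusted against adjusted regression: effect of covariate adjustment.

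Base statements about robustness or method choice on steps 2 and 3. If the extra runs are not done, reword the Discussion and Strengths and limitations to claim only whether both analyses reach the same cost-effectiveness verdict. The derivation of the ceiling ratio can stay as planned.

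The cost is one extra simulation and one extra regression per state, so two of each in all, with no new data. The robustness claim may turn out more modest.
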